# Rationale and design of the Caloric Restriction and Exercise protection from Anthracycline Toxic Effects (CREATE) study: a 3-arm parallel group phase II randomized controlled trial in early breast cancer

**DOI:** 10.1186/s12885-018-4778-7

**Published:** 2018-09-03

**Keywords:** Anthracyclines, Cardiotoxicity, Breast cancer, Exercise, Caloric restriction, Magnetic resonance imaging

## Abstract

**Background:**

Anthracycline chemotherapy agents are commonly used to treat breast cancer, but also result in cardiac injury, and potentially detrimental effects to vascular and skeletal muscle. Preclinical evidence demonstrates that exercise and caloric restriction can independently reduce anthracycline-related injury to the heart as well as cancer progression, and may be promising short-term strategies prior to treatment administration. For women with breast cancer, a short-term strategy may be more feasible and appealing, as maintaining regular exercise training or a diet throughout chemotherapy can be challenging due to treatment symptoms and psychosocial distress.

**Methods:**

The Caloric Restriction and Exercise protection from Anthracycline Toxic Effects (CREATE) study will determine whether acute application of these interventions shortly prior to receipt of each treatment can reduce anthracycline-related toxicity to the heart, aorta, and skeletal muscle. Fifty-six women with early stage breast cancer scheduled to receive anthracycline treatment will be randomly assigned to one of three groups who will: 1) perform a single, 30-min, vigorous-intensity, aerobic exercise session 24 h prior to each anthracycline treatment; 2) consume a prepared diet reduced to 50% of caloric needs for 48 h prior to each anthracycline treatment; or 3) receive usual cancer care. The primary outcome is magnetic resonance imaging (MRI) derived left ventricular ejection fraction reserve (peak exercise LVEF – resting LVEF) at the end of anthracycline treatment. Secondary outcomes include MRI-derived measures of cardiac, aortic and skeletal muscle structure and function, circulating NT-proBNP, cardiorespiratory fitness and treatment symptoms. Exploratory outcomes include quality of life, fatigue, tumor size (only in neoadjuvant patients), oxidative stress and antioxidants, as well as clinical cardiac or cancer outcomes. MRI, exercise tests, and questionnaires will be administered before, 2–3 weeks after the last anthracycline treatment, and one-year follow-up.

**Discussion:**

The proposed lifestyle interventions are accessible, low cost, drug-free potential methods for mitigating anthracycline-related toxicity. Reduced toxic effects on the heart, aorta and muscle are very likely to translate to short and long-term cardiovascular health benefits, including enhanced resilience to the effects of subsequent cancer treatment (e.g., radiation, trastuzumab) aging, and infection.

**Trial registration:**

ClinicalTrials.gov NCT03131024; 4/21/18.

## Background

Anthracycline chemotherapy agents are one of the most widely used and highly active classes of anticancer therapies for numerous cancer types, including breast, lymphoma, leukemia, uterine, ovarian, and lung cancers [1, 2]. However, anthracyclines are associated with cardiomyocyte damage that may be immediate, cumulative, and synergistic with other cancer treatments [3, 4]. This damage manifests as cardiotoxicity, which is diagnosed by a > 10 percentage point drop in left ventricular ejection fraction (LVEF) from baseline to a LVEF < 53% [5]. A recent prospective study reported a 10% incidence of anthracycline-related cardiotoxicity among patients with breast cancer within the first year after treatment [6]. However, prevalence of subclinical cardiotoxicity, which could be defined by elevated circulating cardiac biomarkers [7] or deterioration in left ventricular (LV) longitudinal strain [8], is likely substantially higher [9]. Subclinical cardiotoxicity may increase susceptibility to future insults, including subsequent receipt of other cardiotoxic cancer therapies, aging, and infection [9].

Anthracycline treatment, in addition to other cardiotoxic breast cancer therapies (i.e. left breast radiation, trastuzumab) play a direct role in the increased risk of cardiovascular disease and related death among women who have had a breast cancer diagnosis relative to those who have not [10–12]. Strategies to reduce anthracycline-related cardiac injury are required to balance the oncologic efficacy with cardiac safety of breast cancer therapy. To date, these have included dose minimization/reduction [9], which may translate to reduced oncological benefit [13], or traditional cardiovascular pharmacological agents [14–16], which can be associated with additional side effects and inadequate adherence.

Lifestyle interventions including exercise training and diet modification are novel non-pharmacological potential cardio-protective therapies. Firstly, exercise training is widely established to ameliorate anthracycline-related cardiac injury in preclinical studies, and cardiovascular risk factors in breast cancer survivors [17]. However, during chemotherapy treatment, breast cancer patients have modest and variable adherence to exercise 3×/week due to treatment symptoms, cancer-related appointments, and travel to the exercise facility [18]. Secondly, nutrient deprivation increases the resistance of healthy cells, but not cancer cells, to the damaging effects of oxidative stress by 1000-fold [19, 20]. This phenomenon, termed ‘selective stress resistance’ could dramatically reduce treatment toxicity. For example, 40 days of a 35% calorie restricted diet led to 100% protection from anthracycline-related cardiotoxicity and death in a preclinical model [21]. However, this type of long-term caloric restriction regimen is likely unfeasible for individuals during chemotherapy as they typically suffer from malnutrition, psychological distress, and other treatment complications [22]. Therefore, given that potential for universally high adherence among all patients is important for interventions to achieve far-reaching effects, more feasible methods of lifestyle intervention are required during chemotherapy for breast cancer.

Short-term administration of exercise and caloric restriction shortly prior to receipt of anthracycline treatment capitalizes on the potentially critical, yet underappreciated protective factor of intervention timing, and may ameliorate the issue of inadequate adherence to longer interventions. Based on preclinical evidence [23, 24], we previously investigated the effect of 30 min of vigorous-intensity treadmill walking performed 24 h prior to every anthracycline treatment (i.e., one session per 2–3 week cycle) on markers of cardiotoxicity and treatment symptoms in women with breast cancer [25, 26]. This is a highly feasible approach as patients are usually scheduled to attend the treatment center for blood tests and physician examination the day prior to treatments and this day would also correspond with the nadir of symptoms from the previous treatment. We found that, in contrast to exercise training during chemotherapy, there was 100% adherence to the acute intervention, and no adverse events. Further, the exercise session significantly attenuated NT-proBNP at 24–48 h after the first treatment, which is a circulating biomarker of anthracycline-related cardiac damage and cardiac events. At treatment completion, performing the session prior to each therapy had prevented an increase in resting heart rate (highly prognostic of mortality) and cardiac output, and reduced body weight and prevalence of sore muscles, low back pain and depressed mood relative to usual care [25, 26].

Preclinical studies have reported that 1–2 months of mild caloric restriction or short periods (24–60 h) of more severe caloric restriction or fasting may be effective to prevent cardiac and other toxicities from supraclinical chemotherapy doses [20, 22, 27]. While the effect of caloric restriction on chemotherapy-related side effects has not been studied in women with breast cancer, a pilot study of a complete fast for 24 h prior to and 24 h after anthracycline treatment was well tolerated and reduced hematological toxicity, but cardiovascular function was not measured [28]. Based on this available evidence, 48 h of 50% caloric restriction is likely to provide protection against the much lower clinical doses given each treatment cycle for humans and be well tolerated and safe for women receiving chemotherapy for breast cancer. Overall, there is promising preliminary evidence that acute exercise or caloric restriction could be feasible and effective methods to reduce anthracycline-related cardiotoxicity and treatment symptoms.

Preclinical evidence suggests anthracycline-related toxicity is not confined to the heart, but similarly affects the vessels and skeletal muscle [29]. Available studies in humans are limited in depth and methodology, and lack an integrative approach to characterizing all of these related tissues in the same patients. Considering the established role of vascular and skeletal muscle pathophysiology in traditional heart disease [30, 31], these treatment toxicities likely play a role in the increased risk of cardiovascular disease and exercise intolerance, as well as experience of fatigue, reduced quality of life, and overall health among breast cancer survivors. Both exercise and caloric restriction have the potential to modify anthracycline-related vascular and skeletal muscle dysfunction via modulation of inflammation, cellular apoptosis [32–34], oxidative stress, and endothelium-dependent vasodilation (i.e., nitric oxide bioavailability) [35, 36].

Additionally, both caloric restriction and exercise have antineoplastic effects and can potentially sensitize the tumor to chemotherapy [22, 37], further reducing mortality risk in individuals diagnosed with cancer. Although substantial epidemiological evidence has established the relationship between physical activity and cancer prevention and recurrence [38], experimental evidence exists primarily in preclinical models. Likewise, caloric restriction has been widely established to suppress carcinogenesis in over 40 preclinical studies, yet experimental evidence in human cancer patients is limited [39]. These interventions could also be hypothesized to have positive effects on fatigue, chemotherapy symptoms, and health-related quality of life, given the potential benefit on organ systems integral to health.

The Caloric Restriction and Exercise protection from Anthracycline Toxic Effects (CREATE) study aims to determine if short-term application of aerobic exercise or caloric restriction prior to each anthracycline chemotherapy treatment for breast cancer will reduce the detrimental effects of anthracyclines on the heart, vessels and skeletal muscle and treatment symptoms. The exploratory aims are to determine the effect of the interventions on tumor size, quality of life, fatigue, oxidative stress, and clinical cardiac and cancer outcomes.

## Methods

### Design and ethics

The CREATE study is a three-arm, parallel group phase II randomized controlled trial that will compare the effects of a single aerobic exercise session performed 24 h prior to each anthracycline treatment, to 50% caloric restriction for 48 h prior to each anthracycline treatment, to usual care on cardiac, vascular, and skeletal muscle changes in women with breast cancer. The overall study design is summarized in Fig. 1. The Health Research Ethics Board of Alberta (HREBA) Cancer Committee approved this study and all participants will provide written informed consent. Confidentiality of potential and enrolled participants will be protected by access being restricted to study staff only. All protocol amendments will be approved by the HREBA and updated on clinicaltrials.gov [40].

**Fig. 1 Fig1:**
[figure not shown]
Study design. Note: Most patients at the Cross Cancer Institute will receive three anthracycline cycles total, followed by additional chemotherapy treatments (typically taxanes). In the case where patients receive more than three anthracycline treatments, the intervention will be applied to all cycles received

### Randomization

Randomization will consist of a permutated block design with random block sizes of six and nine and stratification by two factors with a 1:1:1 allocation ratio. The stratification factors will include: 1) receipt of trastuzumab (yes/no), as it is also known to affect cardiac function; and 2) adjuvant/neoadjuvant protocol to ensure an equal distribution of neoadjuvant patients to assess the exploratory tumor size outcome. An external party to the study will generate the randomization sequence using a spreadsheet random function. This same individual will put the group assignment into sequentially numbered, sealed, opaque envelopes. Randomization will occur following completion of baseline assessments.

### Participants

Potential participants will be identified and screened at new breast cancer patient medical oncology clinics at the Cross Cancer Institute in Edmonton, Alberta, Canada, the largest cancer treatment center serving Northern Alberta. Eligibility criteria are listed in Table 1. Participants will sign the consent form with and be assigned to a group by the same investigator. Participants will be reimbursed for parking for all required study visits but there is no other compensation for participation.

**Table 1 Tab1:** Participant eligibility criteria

Inclusion criteria	Exclusion criteria
• ≥ 18 years of age • Female • Able to read and communicate in English • Diagnosis of stage IA-IIIC breast cancer • Scheduled to receive anthracycline-containing chemotherapy • Willing and able to adhere to either intervention	• Contraindications to research MRI (e.g. pacemaker, magnetic implant) • Contraindications to maximal exercise testing • Pregnancy • Limitations to sustained exercise on all potential modes (i.e., treadmill, elliptical, bike) • Body mass index <19 kg/m^2^ or history of eating disorder • Diabetes • Severe food allergies or diet restrictions

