### Blinding

It will not be possible to blind participants or interventionists to their group assignment. It is unlikely that the lack of blinding will influence the primary and secondary physiological outcomes but it could potentially influence the patient-reported outcomes. Study staff that are blinded to group assignment and prior test results will perform CPETs and circulating biomarker analyses. All MRI analyses (i.e. the quantification of data from the images) where user input can impact data (e.g., LV volume tracing) will be blinded to group assignment and time point using random numbers.

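### The investigator who takes consent also assigns the group, so in this open, blocked, single-centre trial the next allocation is partly predictable at recruitment

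*Protocol article*

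**What the plan says.** The Randomization section sets out several sound safeguards. On the scheme: "Randomization will consist of a permutated block design with random block sizes of six and nine and stratification by two factors", allocated 1:1:1. The factors are trastuzumab (yes/no) and adjuvant/neoadjuvant protocol, which gives four strata. On generation: "An external party to the study will generate the randomization sequence using a spreadsheet random function". On concealment: "This same individual will put the group assignment into sequentially numbered, sealed, opaque envelopes". On timing: "Randomization will occur following completion of baseline assessments".

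The Participants section then gives the last step to the recruiter: "Participants will sign the consent form with and be assigned to a group by the same investigator". The same section names a single cancer centre as the place of recruitment.

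The Blinding section states: "It will not be possible to blind participants or interventionists to their group assignment". It provides blinding for the MRI analyses, exercise tests and biomarker assays. Nothing in the article keeps past allocations from the person who recruits.

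**The concern.** An opaque envelope hides the next card. It does not hide what earlier cards in the same stratum imply about it. In blocked randomisation an arm that has come up less often so far is more likely to come next, and a person who makes the assignments in an open trial sees what has come up. If that person also takes consent, the expectation is present when a woman is approached, encouraged or left aside, and it can act without any intent.

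There is some room for judgement. One inclusion criterion in Table 1 asks whether the woman is willing and able to follow either intervention. The Discussion accepts that timing will keep some eligible patients out. The primary outcome is measured at peak exercise, to volitional exhaustion, so fitness and motivation could plausibly relate to it. About 15 evaluable women per arm are planned (Sample size determination), so a few selective enrolments could matter. Blinded image reading protects how the outcome is measured, not who enters which arm.

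**Working it through.** The article states no figure for predictability, so there is none to reproduce. The enrolment total used below is its own: 15 × 3 = 45 evaluable, 45 / 0.80 = 56.25, stated as 56.

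**Inputs from the article**
- 56 patients, three arms, 1:1:1.
- Permuted blocks of 6 or 9, size varied at random.
- Two binary factors, so four strata.
- The person who consents also assigns; allocation is open.

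**Assumptions, not in the article**
- Block sizes 6 and 9 are equally likely.
- Stratum sizes: 14/14/14/14, 28/16/8/4 or 34/10/8/4.
- The guesser knows the stratum and every past allocation in it.

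**Formula.** Let b be the current block size, c_j the number already given to arm j in the block, and w(b, c) the probability of that state given the stratum's history. Then

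P(next = j) = Σ w(b, c) × (b/3 − c_j) / (b − Σc).

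The weights are updated by Bayes' rule after each assignment, and the best guess is the arm with the largest P.

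**One case by hand.** Suppose the first five assignments in a stratum are exercise, exercise, diet, diet, usual care.
- Likelihood if b = 6: (2/6)(1/5)(2/4)(1/3)(2/2) = 1/90.
- Likelihood if b = 9: (3/9)(2/8)(3/7)(2/6)(3/5) = 1/140.
- Probability that b = 6: (1/90) / (1/90 + 1/140) = 140/230 = 0.61.
- P(usual care next) = 0.61 × 1 + 0.39 × 2/4 = 0.80.

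A person who knows no block sizes and simply picks the arm used least so far makes the same guess.

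**Whole trial, by simulation (1,500 to 2,000 trials per setting, four strata)**

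| Quantity | Result |
|---|---|
| Best guess correct | 51–52% (chance 33%) |
| Next arm certain | about 4%, or 56 × 0.04 ≈ 2 patients |
| At least one arm ruled out | about 12% |
| Some arm has probability ≥ 0.5 | 38–40% |
| Least-used-arm guess, block sizes unknown | 51–52% |
| Best guess if one other patient in the stratum is randomised between consent and assignment | about 44% |

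**Upper bounds.** If all 56 patients fell in one stratum, the guess would be right about 54% of the time, with about 3 of 56 certain. If the current block size were always known, an exact recursion gives 3.367 correct guesses per block of 6 (56.1%) and 4.787 per block of 9 (53.2%). In the long run that is (3.367 + 4.787) / 15 = 54.4%.

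The gain over chance therefore comes from balanced blocks combined with a tally. Knowing that the sizes are six and nine adds almost nothing to the guess rate.

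**The case against.** Much of the procedure is sound: an external party generates the list and fills the envelopes, block size varies, and randomisation waits for baseline. Even the ideal guesser is wrong about 48% of the time. In practice the rate would be lower. Baseline tests fall between consent and assignment, so another patient in the stratum may be randomised meanwhile. The Discussion says some women need further tests before their treatment course is settled, so the stratum may not be known at consent. The wording on the same investigator may mean the same one for each participant rather than one for the whole trial, in which case each would hold only part of the history unless they shared it. The article does not say who decides whom to approach. Treatment usually starts the week after consultation, which leaves little room to hold a woman back for a later envelope. LVEF reserve is measured before randomisation and modelled longitudinally, so selection that shows in the baseline value would be visible and partly accounted for.

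All of this stands, and it makes the concern modest. It does not remove it. Random block sizes and four strata are already in the 52%. Randomising after baseline stops a reaction to a known assignment but not an expectation at approach or consent. Baseline LVEF reserve does not capture unmeasured motivation.

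**Conclusion.** The concern holds as a modest, avoidable weakness. Combining consent and assignment gives a person with a full tally about a 52% chance of naming the next arm instead of 33%, with certainty for about 2 of 56 patients. This rests on assumed stratum shares, equally likely block sizes and a complete tally, so it is close to a ceiling for the four-stratum design.

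Three stronger readings are tempting and not supported.
- A reader might infer that stating the block sizes is what makes allocation guessable. The guess rate is about the same without knowing them.
- A reader might infer that favouring fitter women when exercise is expected would bias both comparisons with usual care. That behaviour shifts the exercise comparison and leaves diet versus usual care about where it was. Shifting both needs a different behaviour, namely selecting on whether usual care is expected.
- A reader might want a bias in SD units. That would need an assumed difference between selected patients, for which the article gives no source, a tally acted on for every patient, and no allowance for the baseline measurement. The size of the bias cannot be derived from the document.

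Nothing here suggests that selection has occurred or is intended.

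**What to change.** Amend the Participants section so that the person who screens and takes consent does not assign. Once baseline assessments are confirmed complete and the stratum is given, either the external party who already generates the sequence and fills the envelopes, or an existing staff member with no part in recruitment, opens or releases the next envelope for that stratum. The assignment goes straight to the intervention staff. The recruiter is given no running list of allocations. The block scheme need not be changed or regenerated.

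The cost is a one-paragraph amendment using people already available to the trial. The drawback is availability for about 56 releases in a short window: the Discussion requires baseline to be finished at least 72 h before the first treatment, and the diet to be delivered by 48 h before it. Eligibility, interventions, sample size and analysis do not change. The amendment helps only those still to be enrolled, and analysis cannot fully repair selection that has already happened.

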### Outcome measures

The study outcome measures and their timing are summarized in Table 2. The primary outcome measure is cardiac function reserve capacity (LVEF reserve), which is calculated as peak exercise LVEF – resting LVEF, at the end of anthracycline treatment relative to the control group. Despite being the primary parameter used to diagnose cardiotoxicity, it is recognized that resting LVEF is insensitive to subclinical anthracycline-related cardiac damage due to the heart’s capacity to compensate for dysfunction at rest. By the time a decrease in resting LVEF is realized, there is likely already substantial and irreversible damage to the myocardium [3]. In women previously treated for breast cancer, a systematic review demonstrated that the application of either exercise or pharmacological stress during cardiac imaging techniques identified cases of cardiac dysfunction that were not identified using resting imaging [41]. More specifically, in women receiving anthracycline treatment for breast cancer, LVEF reserve (peak – rest) and peak LVEF after two treatments were significant predictors of a resting LVEF drop to < 50% at 18 months after treatment [42].

**Table 2 Tab2:** Summary of study outcome measures

Measure	Assessment Method	72+ h pre-anth	24 h post 1st & last anth	2–3 w post last anth	1 y post 1st anth	5 y post 1st anth
Primary Outcome:						
LVEF reserve (peak – rest)	MRI	x		x	x	
Secondary Cardiac Outcomes:						
Peak and resting LVEF	MRI	x		x	x	
Resting and peak LV strain	MRI	x		x	x	
LV volumes and cardiac output	MRI	x		x	x	
Myocardial T1	MRI	x		x	x	
LV mass	MRI	x		x	x	
NT-proBNP	Venipuncture	x	x	x		
Secondary Vascular Outcome:						
Ascending and descending aortic distensibility	MRI	x		x	x	
Secondary Skeletal Muscle Outcomes:						
Lower leg oxygen extraction	MRI	x		x	x	
Lower leg oxygen consumption	MRI	x		x	x	
Thigh muscle mass	MRI	x		x	x	
Thigh muscle quality	MRI	x		x	x	
Secondary Integrative Outcomes:						
Whole body oxygen consumption reserve	CPET	x		x	x	
Treatment symptoms	Rotterdam Symptom Checklist	x		x	x	
Exploratory Outcomes:						
Tumor size	Ultrasound	x		x^a^		
Quality of life	FACT-General questionnaire	x		x	x	
Fatigue	FACT-Fatigue questionnaire	x		x	x	
Markers of oxidative stress/antioxidants	Venipuncture	x		x		
Clinical Outcomes					x	x
Safety Outcomes:						
Clinically reported symptoms	ESAS	Will be extracted from clinical records for intervention period				
Intervention-related symptoms or adverse events	Food diary, Exercise session log	Will be collected for each intervention delivered				

*anth* anthracycline chemotherapy treatment, *CPET* cardiopulmonary exercise test, *ESAS* Edmonton Symptom Assessment System, *LVEF* left ventricular ejection fraction

^a^Typically measured before and after completion of all chemotherapy as standard of care

Secondary outcome measures include other parameters of cardiac function and structure (LV resting and peak strain, myocardial T1, LV volumes and mass, resting and peak cardiac output, peak LVEF, resting LVEF) and aortic distensibility at the end of anthracycline treatment, as well as circulating NT-proBNP at 24 h post the first and last treatment. Secondary skeletal muscle outcome measures include lower leg oxygen consumption and extraction, and thigh mass and quality at the end of anthracycline treatment. Secondary integrative outcome measures include whole body oxygen consumption reserve and treatment symptoms. Both interventions are hypothesized to reduce toxic effects on the heart, aorta, skeletal muscle and integrative measures relative to usual care.

A number of additional outcome measures of interest will be collected that are designated as exploratory. Exploratory outcomes at end of treatment include: 1) tumor size in neoadjuvant patients; 2) patient-reported quality of life and fatigue; 3) circulating markers of oxidative stress and antioxidants. To assess for potential longer-term effects of the interventions, a one-year follow-up with assessment of all MRI and questionnaire measures as well as CPETs and clinical outcomes (e.g. cancer recurrence, cardiac events, hospitalizations, mortality) will be completed. These combined clinical outcomes will also be collected as exploratory outcomes after five years of follow-up.

Safety outcomes will include clinically reported Edmonton Symptom Assessment scores throughout the intervention period as well as intervention-related symptoms or adverse events collected via food diaries and supervised exercise session monitoring.

